## Abstract

**Background:**

Liver cirrhosis leads to an impaired liver function with reduced metabolic capacity, which affects the pharmacokinetics of several drugs, requiring dose adjustments. Although limited literature provides guidance on appropriate administration of drugs in cirrhosis, no guidelines currently exist for dose selection or adjustment.

**Objective:**

The objective of this study is to provide guidance on the selection, dosing, and appropriate use of drugs in patients with liver cirrhosis and evaluate the clinical application of these recommendations.

**Methods:**

Three steps are planned to establish dose recommendations for patients with liver cirrhosis. First, a systematic literature search will be conducted to identify specific recommendations for drug selection and dosing in cirrhosis, and the literature will be assessed for reporting quality and evidence level. Subsequently, the resulting recommendations will undergo an internal preassessment procedure for relevance of the covered drugs with regard to availability, the clinical impact of adverse drug reactions, the frequency of use, and the expected benefit of dose adjustment. Second, a modified Delphi procedure will be conducted to (1) analyze the clinical handling of the identified drugs by experts in clinical practice in a first round and (2) parse changes resulting from the inclusion of medication-related information and further harmonize differing dose recommendations in a second round. Finally, the adopted dose recommendations will be implemented in a clinical study involving patients with liver cirrhosis to analyze the impact of the recommendations on patient safety.

**Results:**

The planned clinical validation phase started in January 2025 and is currently underway. As of May 2026, 121 patients have been enrolled. Statistical analyses will be conducted in accordance with the predefined analysis plan. Findings from the literature review, the Delphi consensus process, and the clinical validation phase will be reported in subsequent publications. Final study results and data analysis are anticipated in August 2026.

**Conclusions:**

This protocol outlines a structured approach combining a systematic literature review of specific dose recommendations in patients with cirrhosis that integrates a quality assessment to ensure the inclusion of only high-quality evidence, expert opinions through a Delphi consensus aligning differing recommendations, and a clinical validation to support safer drug therapy in patients with liver cirrhosis.

## Introduction

Liver cirrhosis with advanced fibrotic remodeling of the parenchyma as the terminal stage of different chronic liver diseases leads to impaired liver function with reduced metabolization capacity, shunt circulation, and reduced serum protein levels [1,2]. It is classified into 3 grades of severity according to the Child-Pugh scale, which incorporates both objective laboratory (bilirubin, albumin, and international normalized ratio) and clinical (encephalopathy and ascites) parameters that are not easily quantifiable [2]. As the reduced metabolization capacity of the liver affects the pharmacokinetics of several drugs, their doses have to be adjusted. Missing dose adjustment or administration of contraindicated drugs are common medication-related problems (MRPs) [3,4]. It can be assumed that 33% of patients with cirrhosis experience at least one adverse drug reaction (ADR) during their hospital stay due to missing dose adjustments, which may result in a considerable prolongation of hospitalization in affected patients [5]. Of these ADRs, 68% are considered preventable [6]. There is plenty of literature that aims to assist in adequate administration of drugs in this population [7,8]. However, despite the availability of multiple reviews, consensus papers, and guidance documents addressing individual aspects of drug use in liver cirrhosis [6-8], no comprehensive clinical practice guideline for drug selection and dose adjustment across disease stages is currently available. As the Summary of Product Characteristics (SmPC) usually only provides vague information, dose adjustments in patients with hepatic impairment remain challenging in clinical practice [9].

To address this problem, we designed a systematic 3-step approach to identify dose recommendations for drugs in patients with liver cirrhosis via a systematic literature search, standardization of the recommendations using a Delphi consensus method, and direct application of the results to hospitalized patients with cirrhosis in a clinical study. The aim of this study is to provide support for the choice of an appropriate active substance within a therapeutic class (drug selection) and dose adjustment, as well as additional guidance for the use of drugs in cirrhosis. In contrast to the existing drug-specific safety classifications and database by Weersink et al [7], this study focuses on the harmonization of published dosing recommendations through a structured, multidisciplinary Delphi process and the subsequent real-world application of these consensus-validated recommendations in a prospective, pharmacist-led clinical intervention.

## Methods

### Overview

Three steps are planned to transfer dose recommendations for drugs from the literature via consensus validation to clinical application in patients with liver cirrhosis (Figure 1). The different study components are reported in accordance with established reporting guidelines. The systematic literature phase is mapped to the PRISMA (Preferred Reporting Items for Systematic Reviews and Meta-Analyses) 2020 guidelines; the Delphi consensus process is mapped to the CREDES (Guidance on Conducting and Reporting Delphi Studies) checklist; and the clinical validation phase is mapped to the SPIRIT (Standard Protocol Items: Recommendations for Interventional Trials) 2013 guidelines, including the SPIRIT-Outcomes extension.

**Figure 1. F1:**
[figure not shown]
Flowchart of the process: transferring dose recommendations from the literature to clinical application. DRP: drug-related problem.

### Compilation of Dose Recommendations

#### Structured Search and Selection of the Literature

The details of the identification of relevant evidence on dosing recommendations for patients with liver cirrhosis via a systematic literature review, including the search strategy, screening workflow, and inclusion and exclusion criteria, have recently been published [10]. In brief, structured searches of PubMed and Embase were conducted to identify peer-reviewed publications providing explicit dosing recommendations for patients with liver cirrhosis (Textbox 1). Only publications offering specific and clinically actionable guidance beyond the SmPC were considered eligible. This approach focused on already formulated dosing guidance rather than on isolated primary pharmacokinetic studies to ensure comparability across substances and alignment with real-world prescribing practice.

Textbox 1.Original search strings for the PubMed and Embase databases used in the structured literature search.
**Search string 1**
Search: ((liver) OR (hepatic)) AND ((impairment) OR (dysfunction) OR (damage) OR (injury)) AND ((dose) OR (dosage)) AND ((recommendation) OR (adjustment) OR (modification) OR (adaptation))
**Search string 2**
Search: (recommendation) AND (drug) AND ((prescription) OR (dosage) OR (safety)) AND ((liver) OR (hepatic)) AND ((cirrhosis) OR (disease) OR (impairment))

#### Assessment of Reporting Quality and Evidence Level

Reporting quality was evaluated to determine whether the derivation of dosing recommendations was sufficiently transparent and reproducible. Evidence levels were assigned according to the Oxford Centre for Evidence-Based Medicine framework [11]. Reporting checklists (PRISMA for systematic reviews [12], AGREE [Appraisal of Guidelines for Research and Evaluation] for guidelines [13], and CREDES for Delphi procedures [14]) were applied to assess transparency and reproducibility of reporting rather than intrinsic scientific validity or clinical relevance. Publications were excluded only in cases of major reporting deficiencies that prevented understanding or reproduction of how dose recommendations were derived. References with minor or moderate reporting limitations were retained, and their reporting shortcomings were documented with the assigned evidence level [10].

#### Extraction and Analysis of Information for Each Active Substance

From the included publications, only recommendations allowing for direct clinical application (eg, clear dose adjustments, interval modifications, avoidance statements, or specification of no adjustment required) were considered. Drug classes requiring highly individualized and indication-specific dosing decisions (eg, cytostatics) were excluded as treatment protocols for these agents are typically governed by specialized oncology guidelines and do not permit generalized dose recommendations across patient groups. The extracted recommendations were structured according to active substance and, where available, stratified using the Child-Pugh classification [15,16] to enable direct comparison and consensus validation. Where multiple publications provided differing recommendations for the same active substance, statements were compared to assess consistency. The resulting structured compilation of dosing recommendations served as the basis for the subsequent Delphi consensus process. A detailed description of the comparative methodology is available in the original systematic review [10].

### Definition of Consensus-Validated Dose Recommendations

#### Internal Preassessment Concerning the Clinical Relevance of Expected ADRs

As the systematic literature search was carried out without restrictions on the publication date, the identified active substances will be cross-checked for relevance against the stock list of the pharmacy of University Hospital Bonn, including all drugs and medical devices used by the wards of the Department of Internal Medicine I. Active substances not included in the pharmacy stock list of this hospital of maximum care will be excluded from further processing as their absence indicates that they are not used regularly in clinical practice. However, before the medications are removed, their clinical relevance will be checked again by 2 pharmacists.

For feasibility reasons, and to focus on active substances particularly relevant in cirrhosis, a preselection will be conducted through an internal preassessment procedure to rate (1) the relevance of dose adjustments of each active substance considering the severity of potential ADRs mentioned in the literature, (2) the frequency of prescription particularly in patients with cirrhosis, and (3) the expected benefit of dose adjustment to avoid possible side effects. The expert panel will consist of 2 hepatologists and 1 clinical pharmacologist. Each expert will have specific expertise in the treatment of patients with liver cirrhosis. The following data from the selected literature will be the basis for the evaluation: (1) the authors’ recommendations and their justification; (2) further information from the references on hepatotoxicity and ADRs; (3) information from the corresponding SmPC on precautions, hepatotoxicity, and ADRs; and (4) information from the LiverTox database, assigned to category A, B, C, D, or E* in the Categorization of the Likelihood of Drug-Induced Liver Injury. For analysis of the assessments, the 3 different criteria (clinical relevance of ADRs, frequency of use, and expected benefit of dose adjustment) will be weighted in a ratio of 3:1:2. Considering the point scale from 0 to 3 provided to the experts, a maximum of 18 points per active substance can be achieved. Only the most relevant active substances rated, reaching a predetermined minimum score of 13.5 points, will be included for further processing. The cutoff is pragmatically predefined to focus on substances with the highest expected clinical impact and to improve the feasibility of the consensus evaluation.

#### Delphi Survey on the Dose Recommendations

The Delphi technique is a well-established method for the evaluation and assessment of controversial issues by experts, with the aim to produce reasonably reliable consensus-validated statements [14,17]. A Delphi procedure will be conducted that meets the three basic characteristics: (1) anonymity (the 2-round consensus process will be conducted anonymously; the list of participants will only be disclosed to the experts after the evaluation has been completed), (2) iteration (2 interlinked sequential rounds will be carried out), and (3) controlled feedback (in the second round, participants will receive both the consensus results from the first round and their own initial responses, allowing them to reconsider and, if necessary, adjust their assessments; in this way, convergence of evaluations from the first to the second round can be achieved). Unlike the classic Delphi approach, additional information will be provided to the experts in the second round, which they can incorporate into their assessments. This approach allows experts to reconcile their initial clinical judgments with available evidence and formal guidance.

A total of 12 experts with particular expertise in drug safety in hospitalized patients with cirrhosis and involved in drug decision-making processes in hospitals were recruited: 6 (50%) hepatologists, 3 (25%) clinical pharmacologists, and 3 (25%) clinical pharmacists. The assessment sheets will undergo pretesting in 2 rounds by a pharmacist, a clinical pharmacologist, and 2 hepatologists to identify any issues related to understanding and processing of the sheet, resulting in the final version.

According to the rules of the Association of the Scientific Medical Societies for structured consensus in Germany, a recommendation will be considered accepted if at least 75% of the voting experts agree; Table 1 provides a concise overview of the agreement thresholds and decision categories applied. In contrast, divergence will be assumed if (1) no majority consensus is reached, (2) a majority is achieved but at least one-third of the votes indicate a conflicting recommendation (eg, standard dose vs avoidance), and (3) the majority rejects the evidence but no consensus on an alternative approach can be reached (this item only applies to the second round).

**Table 1. T1:** Grade of consensus.

Grade of consensus	Acceptance (%)	Experts (N=12), n
Strong consensus	≥96	12
Consensus	76‐95	10‐11
Majority approval	51‐75	7‐9
No majority approval	≤50	≤6

#### First Round of the Delphi Survey: Usual Prescription of the Drugs

The first round is intended to capture the usual prescribing practice concerning the choice of an appropriate active substance (drug selection) within a therapeutic class and dose adjustment of a selected drug. In this design, structured external evidence is not provided in the first round to capture routine expert prescribing behavior prior to evidence-informed reassessment in the second round. In this context, the experts will be asked about their common practice with the active substances in an average hospitalized patient with liver cirrhosis who does not have additional comorbidities that are not typically found in patients with cirrhosis. The experts will have the options to select, for each grade of the Child-Pugh classification, whether they usually (1) prescribe the unchanged dose as they do to patients without liver disease (no dose adjustment), (2) make a dose adjustment, or (3) avoid the drug completely. If they select a dose adjustment, the experts will be required to provide the type of dose adjustment (eg, dose reduction, prolongation of the dosing interval, or dose adaptation based on the results of therapeutic drug monitoring [TDM]). A comment field will be provided for each active substance, allowing experts to describe any limitations and specific considerations that appear relevant to them (for the standardized response options used to capture routine prescribing practice, see Multimedia Appendix 1). This assessment yields a valid and unbiased baseline, is itself an objective of the study, and will provide clinically meaningful data on existing prescribing behavior.

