### Application of Dose Recommendations in Patients

#### Objective of the Clinical Study and Study Design

Finally, the feasibility and acceptability of the adopted recommendations for drug selection and dosing in liver cirrhosis will be evaluated through a prospective, nonrandomized clinical study involving patients with liver cirrhosis with the following objectives: (1) improvement of drug therapy safety by applying the consensus-validated therapy recommendations in patients with liver cirrhosis and (2) demonstration of clinical usefulness of the consensus-validated therapy recommendations for patients with liver cirrhosis. For this purpose, dose recommendations will be provided to the pharmacists responsible for the wards with hepatologic patients. If discrepancies between the prescribed medication and the adopted dose recommendations are identified in a patient meeting the inclusion criteria, pharmacists will propose a dose adjustment; substitution with an alternative active substance; or another strategy mentioned in the dose recommendations, such as TDM or enhanced monitoring for adverse reactions. The acceptance of the recommendations remains at the discretion of the prescribing physician. The clinical study will be conducted in the hepatology department of University Hospital Bonn.

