
As an additional unique feature of our approach, the second Delphi round represents a structured re-evaluation under enriched information conditions rather than a purely iterative consensus process. In this context, we plan to specifically provide information about the hepatotoxic effects of the drugs to the experts during the consensus process whenever such data are available [32]. Although Zimmerman [33] reported in 1978 that patients with cirrhosis do not experience drug-induced hepatotoxic effects more frequently than other patients, such events are associated with higher morbidity and mortality due to the preexisting vulnerability. Although only a few publications consider hepatotoxicity in their dose recommendations, we want to analyze whether this information from the literature and the SmPC affects expert decisions regarding dose adjustments. Our modified design of the 2-round consensus procedure allows for the analysis of how clinicians actually manage drug dosing in patients with cirrhosis in the absence of formal guidance and the comparison of how the provision of structured evidence influences expert decisions—a dimension not captured through the conventional approach.

One limitation of our study is the evaluation of a restricted number of drugs. However, we will focus on the drugs with the highest expected clinical relevance for the treatment of patients with liver cirrhosis, determined via reconciliation with the stock list of a hospital of maximum care covering all clinically common drugs and the assessment of relevance based on frequency of use, and on the need for dose adjustments in patients with cirrhosis, determined via an internal consensus procedure. In the future, this initial evaluation could be expanded to additional active substances following the same methodology. The weighting of assessment criteria and the predefined cutoff value for inclusion represent pragmatic thresholds defined to operationalize this prioritization strategy. These parameters are not based on statistical calculations and may limit external validity. As prescribing patterns, formularies, and patient populations may vary across institutions, the prioritization strategy applied in this study may reflect local clinical practice and, therefore, may require contextual adaptation when transferred to other health care settings.

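### Round 1 of the Delphi survey is presented as a valid, unbiased baseline of existing prescribing, but it collects self-reports from a selected, mixed panel in which 3 to 6 of 12 experts may not prescribe

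*Protocol article*

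**What the plan says.** In the protocol article, the section First Round of the Delphi Survey: Usual Prescription of the Drugs gives the aim: "The first round is intended to capture the usual prescribing practice". The question is personal: "the experts will be asked about their common practice with the active substances in an average hospitalized patient with liver cirrhosis". For each Child-Pugh grade the expert states whether he or she usually leaves the dose unchanged, adjusts it or avoids the drug. External evidence is withheld in this round. The section then claims: "This assessment yields a valid and unbiased baseline, is itself an objective of the study", and adds that the round will supply data on prescribing behaviour as it exists.

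The section on the second round builds on this. It plans to examine whether the evidence supports or contradicts prevailing practice. The Discussion says that the two-round design "allows for the analysis of how clinicians actually manage drug dosing in patients with cirrhosis in the absence of formal guidance".

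The panel is described under Delphi Survey on the Dose Recommendations. Its 12 members were chosen for their knowledge of drug safety in cirrhosis and their part in hospital drug decisions. The split by profession is "6 (50%) hepatologists, 3 (25%) clinical pharmacologists, and 3 (25%) clinical pharmacists". Table 1 in that section grades consensus on N=12.

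The section on the objective and design of the clinical study separates two roles. Pharmacists propose changes, and "The acceptance of the recommendations remains at the discretion of the prescribing physician".

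**The concern.** A baseline of prescribing practice needs respondents who prescribe, and it needs some reason to think that they stand for the prescribers whose practice is being described. The panel was recruited on neither ground. The criteria are drug-safety expertise and a part in hospital drug decisions. An expert who does not prescribe can answer a question about usual prescribing only with what he or she would advise.

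At stake are the round 1 objective, which the article names as an objective in its own right, and the reading of the change from round 1 to round 2. If advice and prescribing habit are pooled under the name of prescribing practice, the published gap between practice and evidence may belong to neither group.

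**Working it through.** **Inputs.** Panel of 12, split 6, 3 and 3; consensus grades from Table 1: at most 6 votes, no majority approval; 7 to 9, majority approval; 10 to 11, consensus; 12, strong consensus.

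**Step 1, the plan's own figures.** 6 + 3 + 3 = 12; 6/12 = 50%; 3/12 = 25%; 3/12 = 25%. They reproduce.

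**Step 2, who may not prescribe.** The article states professions only. For the pharmacists, the clinical-study section assigns proposing to the pharmacist and the decision to the prescribing physician. Carrying that over to the pharmacists on the panel is an inference. For the clinical pharmacologists the article states no prescribing role either way. The range is therefore:
- pharmacists only: 3/12 = 25%
- pharmacists and pharmacologists: (3 + 3)/12 = 50%

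**Step 3, effect of pooling.** Let *h* be the number of hepatologists and *o* the number of other experts who choose an option. The pooled share is (*h* + *o*)/12.

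| Situation | Lowest pooled share | Highest pooled share |
|---|---|---|
| All 6 hepatologists agree | (6 + 0)/12 = 50.0%, no majority approval | (6 + 6)/12 = 100%, strong consensus |
| 3 of 6 hepatologists agree | (3 + 0)/12 = 25.0%, no majority approval | (3 + 6)/12 = 75.0%, majority approval |
| 9 prescribers (pharmacologists included), all agree | (9 + 0)/12 = 75.0%, majority approval | (9 + 3)/12 = 100%, strong consensus |

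Read the other way, a pooled 9/12 needs *h* = 9 − *o*. With *o* at most 6, *h* is at least 3, so 9/12 is compatible with anything from 3/6 to 6/6 hepatologists.

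**Step 4, the claims beside the design.** Withholding evidence in round 1 removes one influence on the answers. It does not deal with how the panel was selected, with self-report, or with the mix of roles. The limitations in the Discussion cover the restricted drug list, the weighting and cutoff, the Child-Pugh classification, the average-patient model and the before-after design. They do not mention panel selection, role mix or self-report in round 1.

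**Step 5, reach.** Recommendations are selected in round 2. The sample size uses 35%, taken from historical data of the clinic, and an expected 20%. Neither figure comes from round 1.

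**The case against.** The strongest defence is that the claim was meant more narrowly. The same section also speaks of routine behaviour of experts, and the next section of routine clinical judgment. Unbiased can then be read as not yet influenced by the literature. The forms are pretested by a pharmacist, a clinical pharmacologist and 2 hepatologists, and each substance has a comment field. The response form is in an appendix that is not shown, and a breakdown by profession may be planned in a fuller document. The same 12 experts answer both rounds, so the panel's composition does not differ between them by design.

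Much of this stands, and it rules out several stronger readings:
- A reader might infer that half of the panel do not prescribe. The documents do not say so; 25% to 50% is the supportable range, and all 12 are described as taking part in drug decisions.
- A reader might infer that round 1 does not measure prescribing at all. With 6 to 9 possible prescribers among the 12, that goes too far.
- A reader might expect drug-safety experts to adjust doses more than ordinary prescribers do. Nothing in the article supports a direction of bias.
- A reader might take the range from 6/12 to 12/12 as the size of the error. It shows only what pooling allows.

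The defence does not rescue the wording. The article goes beyond expert judgment to existing prescribing, prevailing practice and what clinicians actually do, and no fuller document would make those published statements correct. Pretesting checks whether the form is understood, not whom the answers represent. A constant panel protects the comparison of rounds within the panel. It does not make the starting point a measure of prescribing.

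**Conclusion.** The point holds in this limited form: the article claims for round 1 a property that its design does not provide, and it does not disclose the gap. The supportable description is self-reported practice or advice from 12 selected experts, of whom 3 to 6 may not prescribe. The lower figure rests on inferring the panel pharmacists' role from the clinical-study section; the upper figure also assumes that the clinical pharmacologists do not prescribe.

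The consequence is confined to the round 1 objective and to how the change between rounds is interpreted. A reader might infer that the final recommendation list or the clinical comparison is undermined. The documents do not support that: round 1 results are fed back to the experts, but the list is decided in round 2, where a mixed panel is a reasonable choice. The primary end point and the 138 per group do not use round 1.

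**What to change.** 1. Replace the valid-and-unbiased description of round 1, and the matching statements in the second-round section and the Discussion, with wording such as *self-reported practice or advice of a selected expert panel*.
2. Report the round 1 result for the 6 hepatologists, plus any other expert who states that he or she prescribes for these patients, separately from the remaining experts as one combined group. Show the change from round 1 to round 2 in the same two groups, descriptively only.
3. Add panel selection, role mix and self-report to the limitations.
4. Keep all 12 votes for the consensus decision.

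The cost is one additional table, the wording changes and a link between profession and the anonymous code. Experts get their own first answers back in round 2, so the answers must already be traceable to a person or code. Stating who prescribes may need one short question to the panel. The prescriber baseline will rest on about 6 respondents and should be given as counts. A finer split by profession is not advisable: groups of 3 say little and strain the anonymity of the process, because the experts are later given the list of participants. If all 3 pharmacologists declare that they prescribe, the remaining group falls to 3, and the same caution applies.
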